### Study Objectives

The primary objectives of this study are as follows:

To describe the prevalence of clinical/subclinical infection and AMR patterns and determine their association with sociodemographic, clinical, and nutritional factors among children aged 6-59 months with uncomplicated SAMTo explore health-seeking behavior, antibiotic usage patterns, and care preferences among caregivers of children aged 6-59 months with uncomplicated SAM and the challenges and facilitators for health care providers in managing these childrenTo assess the efficacy of 7-day amoxicillin versus single-dose azithromycin versus no antibiotic, along with standard nutritional care, in weight gain and nutritional recovery among children aged 6-59 months with uncomplicated SAM

The secondary objective of this study is to compare medication safety (clinical adverse events) and adherence in two intervention arms (amoxicillin and azithromycin).

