An RCT [34] conducted in Kanpur, India, among 100 children with uncomplicated SAM (amoxicillin vs placebo) reported no significant differences in clinical or anthropometric parameters between groups. A systematic review and meta-analysis [24] similarly reported that the evidence on empirical antibiotic usage among children with uncomplicated SAM is weak and may require urgent testing.

The Indian Council of Medical Research’s (ICMR) 2019 “Treatment Guidelines for Antimicrobial Use in Common Syndromes” recommend empirical antibiotic use in common illnesses, such as severe sepsis and septic shock, acute bacterial meningitis, community-acquired pneumonia, and necrotizing fasciitis, only when proven to be beneficial. The guidelines also suggest de-escalating or modifying therapy based on culture and drug susceptibility [35]. There is evidence of acute respiratory infection (ARI; 50%) [36] and diarrhea from the NFHS-5 (7.3%), ARI from the NFHS-5 (2.8%), and fever or ARI from the NFHS-5 (69%) [3]. However, there is no evidence in community-based studies of confirmed bacterial infection among children, and most infections among children aged <5 years are suspected to be of viral origin. A 2004 Lancet review [37] reported that the coverage offered by the aminopenicillins group of antibiotics is only 37% in the case of pediatric sepsis in Southeast Asia and the Pacific region [37].

Considering all this evidence, the rationale behind using empirical antibiotics requires urgent assessment, and there is a dire need for a control arm without antibiotics to assess the efficacy of empirical antibiotics in children with uncomplicated SAM. Therefore, this study aims to (1) estimate the clinical/subclinical infection and AMR patterns among children with uncomplicated SAM; (2) explore health-seeking behavior, antibiotic use, and care preferences among caregivers of pediatric patients and identify challenges and facilitators faced by health care providers in patient management; and (3) compare the effectiveness of single-dose azithromycin, 5-day amoxicillin, and no antibiotic therapy on nutritional recovery and clinical outcomes.

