**Figure 1 figure1:**
[figure not shown]
RCT CONSORT flow diagram for recruitment, follow-up, and endline assessment of participants in the study. CBC: complete blood count; CONSORT: Consolidated Standards of Reporting Trials; DST: drug susceptibility testing; ESR: erythrocyte sedimentation rate; FGD: focus group discussion; hs-CRP: high-sensitivity C-reactive protein; IDI: in-depth interview; RCT: randomized controlled trial; SAM: severe acute malnutrition.

**Table 1 table1:** Timepoints and activities to be carried out during the study.

Activity	Baseline	Enrollment to RCT^a^ (within 7 days of collecting baseline data)	Telephonic follow-up at 15, 45, 75, and 105 days (plus 5 days allowed at each timepoint)	Physical follow-up at 30, 60, 90, 120, and 180 days (plus 5 days allowed at each timepoint)
Consent; appetite test; sociodemographic, nutritional, and health-related information obtained through questionnaires during face-to-face interviews + 4 mL^b^ of blood sample, urine sample, and stool sample for CBC^c^, ESR^d^, culture, DST^e^, hs-CRP^f^, procalcitonin, and anthropometry (height, weight, MUAC^g^)	✓	—^h^	—	—
RCT eligibility assessment, randomization and antibiotic distribution, and IFA^i^ syrup distribution in the case of anemia	—	✓	—	—
Weight, height, MUAC, symptoms of adverse events, any illness, and treatment details	—	—	—	✓
Symptoms of adverse events, any illness, and treatment details	—	—	✓	✓

^a^RCT: randomized controlled trial.

^b^Biological samples will be collected from 606 study participants.

^c^CBC: complete blood count.

^d^ESR: erythrocyte sedimentation rate.

^e^DST: drug susceptibility testing.

^f^hs-CRP: high-sensitivity C-reactive protein.

^g^MUAC: mid-upper arm circumference.

^h^Not applicable.

^i^IFA: iron folic acid.

#### Phase 1

A list of children with uncomplicated SAM will be obtained from the NHTS website through district stakeholders. The children will be visited at their homes to confirm their diagnosis and malnutrition category and will be enrolled into the study after obtaining informed consent from the caregivers. The children’s sociodemographic, nutritional, and health-related information will be obtained through questionnaires and interviews. Under a sterile environment, 4 mL of blood sample will be taken from each child. Two sterile containers will be given to the children to collect urine and stool samples, and those samples will be collected from the caregivers the following day.

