A list of children with uncomplicated SAM will be obtained from the NHTS website. The children will be visited at their homes to confirm their nutritional category. At enrollment, each child will be assigned a unique identification number based on the number in the list. After baseline assessment, children will be randomized using stratified randomization to one of three groups: amoxicillin (5 days, twice a day, 15 mg/kg based on weight band + standard nutritional care), azithromycin (single dose, 20 mg/kg + standard nutritional care), or control (no antibiotics + standard nutritional care). Children with subclinical infection will be randomized to either the amoxicillin or the azithromycin group in a 1:1 allocation ratio. Children without any subclinical infection will be randomized to the amoxicillin, azithromycin, or control group in a 1:1:2 randomization sequence to balance the stratified randomization based on subclinical infection status. The remaining children who will be assessed clinically for uncomplicated SAM, who pass the appetite test, and who are found eligible will be assigned to one of the three groups in a 1:1:1 randomization sequence; these children will be recruited after completion of the phase 1 enrollment. Around 150-200 participants are expected to be recruited after phase 1 enrollment to fulfill the sample size requirement for phase 3.

Three separate randomization sequences of unequal block sizes will be generated. A non–peer-reviewed study [40] from Bangladesh reported that 36% of children with uncomplicated SAM have elevated CRP and α1-glycoprotein. Assuming that 35% of children with uncomplicated SAM might have a subclinical infection [40], a randomization sequence will be generated using online software. The allocation will be concealed centrally in the institute. Based on the intervention plan, study participants and administrators will not be masked in the study.

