#### Follow-Up Visits

Children will be followed up monthly during the intervention, in addition to follow-up postdischarge from the program at 4 and 6 months. Telephone calls will be made once every 15 days to document any illness, medication use, or side effects. Physical visits will be made every 30, 60, 90, 120 and 180 days.

For compliance assessment, empty amoxicillin strips will be collected at 30 days. For azithromycin, single-dose compliance assessment will be performed on the day of enrollment to the RCT. An additional buffer of 5 days will be allowed to collect data at each timepoint. Clinical adverse events of the intervention will be assessed during physical visits and documented over the phone.

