Data analysis will be performed in Stata version 18.0 software using intention-to-treat analysis at the end of the study. Per protocol analysis will also be performed as a secondary analysis at the end of the study. Interim analysis will be part of the quality parameter (at the end of the first year). The WHZ and MUAC will be expressed as mean (SD) or median (IQR) with 95% CIs based on data normality. The presence of bilateral pitting edema will be expressed as proportions with 95% CIs. Independent variables (child’s age in months and mother’s age) will be expressed as mean (SD) or median (IQR) with 95% CIs based on data normality. Factors such as education status, type of delivery, and birth complications will be expressed as proportions with 95% CIs. Outcomes such as episodes of acute illness, day care absenteeism, parenteral absenteeism, number of hospital visits, and food consumption will be expressed as mean (SD) or median (IQR) with 95% CIs based on data normality. Outcomes such as the presence of sepsis and mortality status will be expressed as proportions with 95% CIs. The chi-square test will be performed to analyze the association between outcomes and categorical independent variables. An unpaired *t* test (or Mann-Whitney *U* test) will be performed to assess the association between outcomes and continuous independent variables. Poisson regression analysis (bivariate and multivariate) will be conducted to explore the association between dependent and independent factors. Adjusted risk ratios with 95% CIs will be reported for factors included in the multivariate Poisson regression model.

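### No antibiotic-versus-control comparison of adverse events is planned, although the same symptoms are scheduled for collection in all three arms

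*Protocol article*

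**What the plan says.** Study Objectives gives the trial one secondary objective: to "compare medication safety (clinical adverse events) and adherence in two intervention arms (amoxicillin and azithromycin"). Control is not named. The efficacy objective in the same section names all three arms.

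The secondary outcomes (Outcomes) include adverse events, but only those attributed to antibiotic treatment. The same list has morbidity episodes (fever, diarrhea, respiratory symptoms), recurrent infections, transfer to inpatient care and mortality, with no limit by arm.

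Table 1 schedules "symptoms of adverse events, any illness, and treatment details" at the physical visits and the same items at the telephone contacts, again without limit by arm. Follow-Up Visits adds: "Clinical adverse events of the intervention will be assessed during physical visits and documented over the phone".

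The aims that close the section on the need for a control group compare azithromycin, amoxicillin and "no antibiotic therapy on nutritional recovery and clinical outcomes". For phase 3, Data Entry and Analysis is generic: "The chi-square test will be performed to analyze the association between outcomes and categorical independent variables". It restricts no outcome to two arms and specifies no control contrast for adverse events.

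**The concern.** The no-antibiotic arm is there to show whether empirical antibiotics are needed, and Strengths and Limitations says that the results could support revisiting guidelines. That decision needs the excess of harm over giving nothing as well as the benefit. A comparison of amoxicillin with azithromycin cannot supply it: equal rates in the two arms are compatible with a background rate that is the same or much lower.

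The outcome wording adds to the problem. An event attributed to the antibiotic cannot, by definition, arise in a child given no study antibiotic. The same episode of diarrhea could be recorded as a related adverse event in an antibiotic arm and as morbidity in control. Only a count regardless of cause puts the arms on the same footing. The net direction is not obvious either, since the protocol's own background cites a trial in which amoxicillin lowered the risk of diarrhea.

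**Working it through.** **1. Arms covered by each statement**

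| Place | Arms covered |
|---|---|
| Efficacy objective | three |
| Safety and adherence objective | two (antibiotics only) |
| Adverse event outcome | in effect two, through attribution to the antibiotic |
| Table 1 symptom collection | not restricted |
| Morbidity, inpatient transfer, mortality | not restricted |
| Aims, clinical outcomes | three |

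Restricting adherence to two arms is natural, because control children have no study drug to take. The same reason does not apply to adverse events.

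**2. Which children can be compared with control**

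The protocol gives no calculation for adverse events, so there is no figure of its own to reproduce. Study Procedure (Phase 3) sets three sequences:

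- Infected phase 1 children: "Children with subclinical infection will be randomized to either the amoxicillin or the azithromycin group in a 1:1 allocation ratio".
- Uninfected phase 1 children: "Children without any subclinical infection will be randomized to the amoxicillin, azithromycin, or control group in a 1:1:2 randomization sequence".
- Later recruits (150 to 200 expected): 1:1:1.

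The planning share is also given there: "Assuming that 35% of children with uncomplicated SAM might have a subclinical infection". Assume that all 606 phase 1 children enter the RCT and that 150 are recruited later.

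- Infected: 606 × 0.35 = 212.1, or 106.05 per antibiotic arm and none in control.
- Uninfected: 606 × 0.65 = 393.9.
- Each antibiotic arm, sequences with control: 393.9/4 + 150/3 = 148.5.
- Control: 393.9/2 + 150/3 = 247.0.
- Each antibiotic arm, all sequences: 106.05 + 148.5 = 254.5.

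About 106.05/254.5 = 42% of each antibiotic arm would have no randomized control counterpart. A crude three-arm test on all children would mix the effect of treatment with that of infection status.

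**3. Precision of an antibiotic-versus-control risk difference**

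With a common event rate p, SE = √[p(1−p)(1/148.5 + 1/247.0)] and half-width = 1.96 × SE.

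- p = 0.073: SE = 0.0270, half-width 5.3 points.
- p = 0.20: SE = 0.0415, half-width 8.1 points.

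Both rates are assumptions. The 7.3% is the national survey figure for diarrhea cited in the protocol's background. It is not a rate in children with SAM, nor over 6 months of follow-up.

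**4. Sensitivity to recruitment (half-widths at 7.3% and 20%)**

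| Phase 1 entering | Later recruits | Per antibiotic arm v control, sequences with control | Half-widths (points) |
|---|---|---|---|
| 606 | 150 | 148.5 v 247.0 | 5.3, 8.1 |
| 606 | 200 | 165.1 v 263.6 | 5.1, 7.8 |
| 303 (assumed half) | 150 | 99.2 v 148.5 | 6.6, 10.2 |

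Fewer phase 1 entrants widen the interval if later recruitment stays at 150. If later recruits made up the shortfall, it need not widen, since every later recruit can be allocated to control.

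**The case against.** The strongest objection is that most of what matters is already compared across three arms. Diarrhea, fever, respiratory symptoms, inpatient transfer and death are unrestricted secondary outcomes, the aims cover clinical outcomes in all three arms, and the analysis section limits nothing to two arms. This stands. A reader might infer from the safety objective that the trial cannot say whether antibiotics cause more events than no antibiotic, or that the control data go unused. The documents do not support either inference. The data are scheduled, and the main morbidity and serious outcomes are open to a three-arm comparison. What these outcomes do not cover is adverse events as such.

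The two-drug comparison also answers a question of its own. The rationale cites a pilot trial with fewer adverse events on azithromycin than on amoxicillin, and raises concern about compliance. That justifies keeping the comparison, but not leaving control out of the safety objective.

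A reader might further infer that unmasked staff will judge relatedness. The protocol says that participants and administrators are not masked, but not who attributes events. It leaves the safety reporting mechanism to the implementation plan and provides for an independent monitoring board, so this point does not rest on biased attribution.

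Finally, the choice of effect measure and the form of listings commonly sit in an analysis plan, and their absence here is no fault. The arms named in the objective and the definition of the outcome are different: the protocol states both.

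**Conclusion.** The point holds as a gap in the stated safety objective and outcome, and does not amount to an inability of the design. The protocol plans no antibiotic-versus-control comparison of adverse events, although the schedule collects what is needed and the trial's purpose calls for it. The gap is partial, because several harm-type outcomes are already unrestricted by arm.

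Under the allocation assumptions above, the missing contrast would have a half-width of roughly 5 to 8 points for event rates of 7.3% to 20%, which is informative for moderate excesses but not for small ones. These figures show what the added analysis could deliver; they do not measure an error in the plan. They depend on the 35% infection share, on how many phase 1 children enter the RCT, and on event rates that the documents do not give. Caregivers know the allocation, so open-label symptom reporting remains a limitation of any comparison with control.

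**What to change.** - Reword the secondary objective and the adverse event outcome to clinical adverse events of any cause in all three arms.
- Compare each antibiotic with control by risk difference and 95% CI, within the two sequences that include control (uninfected phase 1 children and later recruits), adjusted for sequence.
- Compare azithromycin with amoxicillin across all sequences.
- Report events judged related to the antibiotic as a descriptive listing.
- Keep adherence as a comparison of the two antibiotic arms.
- Acknowledge open-label symptom reporting as a limitation of the contrasts with control.

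The cost is a change of wording and one further table, with no new data or visits. Results reports that the start of the RCT component is delayed, so the change can be made before that component begins. As a change to outcomes, it would go to the ethics committee and the registry under the protocol's own amendment rule.

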## Methods

### Patient and Public Involvement

Patients and the public were not involved in the trial design. However, children aged <5 years with uncomplicated SAM and their caregivers will participate in the study. Study findings will be shared with caregivers, community stakeholders, and program implementers through dissemination meetings and policy briefs.

### Study Design

This study protocol has been registered with Clinical Trial Registry – India (CTRI/2025/03/082358). The study will be conducted in three phases:

Phase 1: cross-sectional, analytical community-based study with a laboratory componentPhase 2: qualitative study using focus group discussions (FGDs) among caregivers and in-depth interviews (IDIs) of health care providers of children aged <5 years with uncomplicated SAMPhase 3: an open-label, parallel-group RCT

### Study Area

Phase 1 of the study will be conducted in Yadadri Bhuvangiri District, Telangana, India [38]. The district has a population of ~800,000, with 16% urban, 80% rural, and some tribal populations, with ~300 villages and 1 municipal corporation area. According to the 2011 Census, this district had 50,000 tribal people. Every month, ~50 new children with uncomplicated SAM and ~100 children with moderate acute malnutrition (MAM) are identified by *Anganwadi* teachers during routine monthly growth-monitoring drives, and the data are entered on the website of the Nutrition and Health Tracking System (NHTS) of the state government under the Supervised Supplementary Feeding Programme (SSFP) [20]. The identified children are provided with locally available nutrient- and energy-dense food, Balamruthuam Plus, an enhanced ready-to-use therapeutic food. Children with MAM receive this food for 2 months, while children with uncomplicated SAM receives it for 4 months. All children with uncomplicated SAM are administered a weight-adjusted dose of amoxicillin twice daily for 5 days.

Phase 2 of the study will be conducted both in the community and the hospital. In the community, caregivers of children with uncomplicated SAM will be contacted for participation in the FGDs. Caregivers who participate in the quantitative study on clinical/subclinical infections and AMR will be eligible for this phase. In the hospital setting—which includes primary health centers (PHCs), subcenters, and district and tertiary care centers—various health care providers, such as medical officers (MOs), auxiliary nurse midwives (ANMs), and pediatricians, will be contacted to participate in the study. IDIs will be conducted with them.

Phase 3 of the study will be carried out in the community via house-to-house visits, initially in Yadadri Bhuvangiri District and later in further districts as the sample gets saturated.

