### Rationale of the Study

In 2023, the Government of India released the National Protocol for Management of Malnutrition in Children to strengthen the ongoing efforts and commitment to address the challenges of malnutrition [18]. Mission Saksham Anganwadi and Poshan 2.0 was launched to drive the efforts to reduce malnutrition by identifying and managing children aged <5 years with SAM in India [19]. Under this program, peripheral health workers and *Anganwadi* (rural child care center in India) teachers are trained to make initial decisions on the level of inpatient or community-based care, nutrition management, and follow-up care for the identified children aged <5 years with SAM. These children are enrolled for CSAM at *Anganwadi*s and administered empirical amoxicillin for 5 days, twice a day, along with nutritional support for 4 months [20].

Although empirical antibiotics are currently in use, recent studies from the Africa region and one from India have not found them effective in improving nutritional recovery [21]. The potential reason was either a low rate of infection among children with uncomplicated SAM at the time of identification or AMR emergence, making empirical antibiotics ineffective [22-24]. Thus, the context-specific relevance of empirical antibiotics needed to be tested by assessing infection rates among children with uncomplicated SAM at the time of identification and by exploring antibiograms.

In India, a few observational studies in tertiary care hospitals among children with complicated SAM have reported a high prevalence of diarrhea (36%), fever (34%), and pneumonia (43%) [25-27]. However, this evidence does not warrant the use of empirical antibiotics among children with uncomplicated SAM managed at the community level without any clinical symptoms of infection. In addition, there is a lack of evidence on the burden of clinical/subclinical infection among children with uncomplicated SAM in India, and it is important to decide whether empirical antibiotics are necessary for this patient group.

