A study [28] from India among children with sepsis in tertiary care centers reported that 48.2% and 90.3% of the children developed AMR to gentamicin and penicillin G, respectively. Another study [29] among pediatric patients in urban Delhi found high rates of AMR to commonly used antibiotics, such as amoxicillin and cotrimoxazole. Although the studies have reported high AMR prevalence among children, the literature on the burden of AMR among children aged <5 years with uncomplicated SAM in India is limited. Antibiograms and AMR profiles are necessary to decide whether the current choice of amoxicillin for empirical management of children with uncomplicated SAM is relevant.

Empirical antibiotics administered for 7 days can lead to poor medication compliance and suboptimal antibiotic use. In Niger, West Africa, empirical mass administration of a single dose of azithromycin was found feasible in a programmatic setting and was effective in reducing mortality due to meningitis, dysentery, malaria, and pneumonia among children aged <5 years [30,31]. A pilot randomized controlled trial (RCT) in Burkina Faso reported similar weight gain and fewer adverse events in the single-dose azithromycin group compared with the 7-day amoxicillin group [32]. However, azithromycin has not been tested in trial mode among children with uncomplicated SAM, and an RCT among children with uncomplicated SAM would generate evidence on the effectiveness of empirical antibiotics in nutritional recovery and aid in deciding whether a single dose of azithromycin is enough.

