### Sample Size

#### Phase 1

Bhutta et al [8] reported that the rates of clinical infections among children with complicated SAM vary from 15% to 68%. Considering 50% prevalence of lower respiratory tract infection among children with uncomplicated SAM, 95% CIs, 10% relative precision, 1.5% design effect, 10% nonresponse rate, and 5% type I error, we will require 606 participants aged 6-59 months with uncomplicated SAM.

#### Phase 2

A purposive sampling strategy will be followed to select participants. Primary caregivers of children with uncomplicated SAM will be identified based on their volunteerism and participation. Yadadri Bhuvanagiri District comprises four project areas (Bhongiri, Aler, Mothkur, and Ramanapeta), each consisting of multiple sectors and each sector covering 25 *Anganwadi*s [38]. FGDs are planned at the project level to ensure adequate representation across geographic areas and variations in the distribution of children with uncomplicated SAM. Initially, two FGDs are planned per project area; however, considering the larger geographic coverage and higher caseload in two project areas, an additional FGDs will be conducted in each of these areas based on data flow. In total, 10-12 FGDs will be conducted to capture diversity in experiences and practices across the district. Each FGD will include 8-10 participants.

As the aim is also to explore barriers and facilitators related to the management of children with uncomplicated SAM, IDIs are planned to include service providers across different levels of the health system. This approach reflects the continuum of care, as a child with uncomplicated SAM encounters multiple providers at different points within the health system. Therefore, two IDIs will be conducted in each health care worker group: Accredited Social Health Activist (ASHA), *Anganwadi* teacher (center), ANM (subcenter), MO (PHC), and pediatrician (district hospital and tertiary care center).

The data saturation principle will guide the final number of FGDs and IDIs to be conducted. Saturation will be considered achieved when no new themes, patterns, or insights emerge from successive FGDs or IDIs and when there is redundancy in the information obtained. Data collection and analysis will be undertaken simultaneously to monitor saturation, and additional FGDs or IDIs will be conducted, if required.

#### Phase 3

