### Inclusion and Exclusion Criteria

#### Phase 1

The inclusion criteria are (1) age 6-59 months, (2) both sexes, (3) resident of the study area, (4) WHZ≤–3 SD without any signs of complications (uncomplicated SAM), and (5) passing the appetite test.

Children with SAM who have medical complications or infection have loss of appetite due to underlying physiological changes. The appetite test helps identify such children. Every child identified as having SAM during growth monitoring will undergo the appetite test to decide the further course of treatment. In Telangana, Balamrutham Plus is used under the SSFP for the test. The quantity provided varies by age: age 7-18 months, at least 15 g; age 19-36 months, 30 g; and age 37-59 months, 50 g. Children who are able to consume the given quantity are considered to have passed the test and are enrolled in the SSFP; otherwise, they are referred to a nutrition rehabilitation center for further treatment. The test usually takes a short time but may even take up to 1 hour [20].

The exclusion criteria are (1) WHZ≥–2 SD, between –2 SD and –3 SD, or <–3 SD with complications (children with complicated SAM); (2) bilateral pitting edema; (3) congenital anomalies, inborn errors of metabolism, or developmental delay; and (4) malabsorption syndromes.

Children with SAM will be identified from the NHTS through the district health administration. During the study period, all eligible children will be contacted to participate in the study.

#### Phase 2

Primary caregivers of children aged 6-59 months with uncomplicated SAM will be identified based on their volunteerism and participation. Each FGD will include 8-10 participants, and 10-12 FGDs will be conducted, in addition to 2 IDIs in each health care worker group: ASHA, *Anganwadi* teacher (center), ANM (subcenter), MO (PHC), and pediatrician (district hospital and tertiary care center). The number of FGDs and IDIs will be based on the level of information saturation.

#### Phase 3

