The inclusion criteria are (1) age 6-59 months, (2) enrollment in the SSFP/CMAM program, (3) WHZ <–3 SD or MUAC=115 mm, (4) passing the appetite test using Balamrutham Plus, (5) both sexes, (6) available for the entire 6 months of the study period, (7) no edema, (8) no antibiotic use in the past 1 month, (9) no clinical complications requiring antibiotic treatment and/or inpatient care, and (10) primary resident of the catchment area. Children who participate in phase 1 will also be eligible to be part of phase 3.

The exclusion criteria are (1) complicated cases of SAM and (2) antibiotic use in the past 1 month.

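### Phase 1 draws children from a programme list on which amoxicillin is routine, but neither secures sampling before that course nor separates children sampled after it

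*Protocol article*

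**What the plan says.** **Sampling frame.** The protocol's Inclusion and Exclusion Criteria, Phase 1, states: "Children with SAM will be identified from the NHTS through the district health administration". Study Procedure, Phase 1, adds: "The children will be visited at their homes to confirm their diagnosis and malnutrition category and will be enrolled into the study". No maximum time from listing to visit is given.

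**Programme treatment.** Study Area says of the same programme: "All children with uncomplicated SAM are administered a weight-adjusted dose of amoxicillin twice daily for 5 days". Rationale of the Study agrees that enrolled children are "administered empirical amoxicillin for 5 days, twice a day, along with nutritional support for 4 months".

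**Eligibility.** The numbered Phase 1 criteria cover age, sex, residence, nutritional category, complications, appetite, oedema, congenital and developmental conditions, and malabsorption. None concerns antibiotics. The Phase 3 (RCT) criteria do contain such an item: "no antibiotic use in the past 1 month".

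**Analysis.** Data Entry and Analysis, Phase 1, reports clinical infection, subclinical infection and AMR as percentages. It then tests their association with sociodemographic, health and nutritional factors, adjusting by log-binomial regression. Recent antibiotic use is not named.

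**Purpose.** Rationale of the Study wants "infection rates among children with uncomplicated SAM at the time of identification" and adds: "Antibiograms and AMR profiles are necessary to decide whether the current choice of amoxicillin for empirical management of children with uncomplicated SAM is relevant".

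**Timing.** Results says that the RCT is delayed and that Phases 1 and 2 have been initiated.

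**The concern.** The target is the child's state when the programme identifies it. The frame is a list whose members the programme goes on to treat. A child reached after the programme's first dose gives cultures and inflammatory markers that reflect partial or completed treatment.

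The expected directions are fewer positive cultures and, among organisms still growing, more that resist amoxicillin. Both bear on the question being asked. Rationale of the Study offers two explanations for empirical antibiotics showing no benefit, namely few infections or emerging resistance, and amoxicillin given before sampling could mimic either. The drug that may distort the estimate is also the drug whose continued use the estimate is meant to inform.

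The RCT delay sharpens the point. While Phase 1 runs alone, no trial allocation takes the place of the programme course, and the only antibiotic check in the document belongs to the component that has not started.

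**Working it through.** **1. Does the text secure sampling before treatment?**

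| Question | What the protocol gives |
|---|---|
| Who is sampled? | Children on the programme's tracking list, at a later home visit |
| Do listed children with uncomplicated SAM get amoxicillin? | Yes, all of them, for 5 days |
| Is sampling required before the first dose? | Not stated |
| Is the programme course withheld during Phase 1? | Not stated |
| Is there an antibiotic criterion in Phase 1? | No; Phase 3 only |
| Is the analysis split by treatment before sampling? | No |

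**2. The plan's own precision figure.** Sample Size, Phase 1, uses 50% prevalence with "95% CIs, 10% relative precision, 1.5% design effect, 10% nonresponse rate" to reach 606. Reading the design effect as 1.5:

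n = 1.96² × 0.5 × 0.5 / 0.05² × 1.5 = 384.15 × 1.5 = 576.2

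Allowing for 10% nonresponse gives 576.2 / 0.9 = 640.2, or 576.2 × 1.1 = 633.8. Neither is 606; a 5% allowance is (576.2 / 0.95 = 606.5). That is a separate matter. Only the 10% relative precision is used below, as a yardstick.

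**3. How much exposure would matter?** Let p0 be prevalence at identification, f the share sampled after the course began, and r the relative drop in positivity among them. Then

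pooled prevalence = p0 × (1 − f × r), so the relative error is f × r.

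It passes 10% when r > 0.10 / f:

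| f (assumed) | r needed |
|---|---|
| 25% | 40% |
| 50% | 20% |
| 75% | 13% |
| 100% | 10% |

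Take p0 = 35%, the subclinical infection figure assumed in Study Procedure, Phase 3. The pooled values are:

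| f (assumed) | r = 20% (assumed) | r = 50% (assumed) |
|---|---|---|
| 25% | 33.25% | 30.63% |
| 50% | 31.50% | 26.25% |
| 100% | 28.00% | 17.50% |

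The documents give neither f nor r, so these are illustrations. They also give nothing from which to size the effect on resistance; only its direction can be argued.

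**4. Precision if only children sampled before dosing form the main estimate.** The 95% half-width is 1.96 × √(1.5 × 0.35 × 0.65 / n):

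| Share sampled before dosing | n | Half-width (points) |
|---|---|---|
| 100% | 606 | 4.7 |
| 75% | 454 | 5.4 |
| 50% | 303 | 6.6 |
| 25% | 152 | 9.3 |

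If 606 already includes the 10% nonresponse allowance, 606 × 0.9 = 545 children give 4.9 points and half of them (273) give 6.9.

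**5. Yardstick against sampling error.** At 35%, a 10% relative error is 3.5 points, which lies inside the 4.7-point half-width at n = 606. To equal that half-width, f × r must reach 4.65 / 35 = 0.133. Unlike sampling error, this error does not shrink as n grows.

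**The case against.** The strongest reply is that sampling was probably meant to come first. Table 1 puts the appetite test at the same baseline as the blood, urine and stool samples. The criteria section describes that test as deciding what care follows, with enrolment in the feeding programme for those who pass. Table 1 also places antibiotic distribution after baseline. The forecast of 150-200 later RCT recruits implies that 750 − 200 = 550 to 750 − 150 = 600 of the 606 Phase 1 children, or 91-99%, would meet the month-long antibiotic-free rule. This is fair evidence of intent. It does not secure the order: no criterion or maximum interval requires it, and Table 1's antibiotic step belongs to the delayed RCT.

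A second reply is that the questionnaire collects health-related information and the analysis includes health factors, so antibiotic history may be recorded. That may be so. An association test or an adjusted ratio would still leave the headline percentage pooled.

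A third reply is that any size is assumed, and this stands in full. A reader might infer that most Phase 1 children are sampled after treatment, or that the prevalence is wrong by a known amount. The documents support neither, because visit timing is not stated and some or all children may be reached before their first dose.

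A reader might also want to carry the RCT's one-month rule into Phase 1. That goes too far. Antibiotics taken before identification, for a recent illness for example, are part of the child's true state at identification, and removing those children could itself bias the estimate. Only the programme course that follows identification is the problem.

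Nor do the documents show that the RCT recruitment forecast fails. The length of the delay is not given, and Study Area allows expansion to further districts.

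**Conclusion.** The point holds as a gap in the Phase 1 design. The plan samples from a list on which amoxicillin is routine, aims at infection and resistance at identification, and contains nothing that puts sampling before the course or separates children sampled after it began. Followed as written, it can mix the two groups in one percentage.

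The size is unknown. At 35% prevalence the pooled figure falls by 3.5 points when f × r = 0.10 and by about 4.7 points when it is 0.133. If every child is reached before dosing, there is no bias. The directions, infection understated and resistance overstated, rest on the general expectation that recent amoxicillin suppresses growth and selects resistant organisms; no effect size comes from the documents.

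The RCT is largely shielded by its own antibiotic criterion, so the consequence lies mainly with the Phase 1 estimates. This is a cheap improvement, not a flaw that invalidates the study.

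**What to change.** - **Sampling:** take Phase 1 samples before the programme's first amoxicillin dose where possible, and state this in the Phase 1 procedure.
- **Recording:** for every child, record the start date of the programme course relative to sampling. Record any other antibiotic in the past month separately.
- **Analysis:** report infection and AMR prevalence split by whether the programme course had begun before sampling. Use children sampled before it as the main estimate at identification. Show other prior antibiotic use only as a descriptive split or sensitivity analysis, not as an exclusion.

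The cost is a few questionnaire fields and one split in the Phase 1 tables. If the questionnaire already holds the dates, only the split and the timing statement are new. Phase 1 has been initiated, so the fields should be added soon, while caregivers and programme records can still supply dates.

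The statistical price is a smaller main denominator: about 6.6 points instead of 4.7 if half of 606 qualify. If few children are undosed when visited, those who remain may be a selected group (newly listed, missed by the programme or not taking the course). Splitting would then not be enough, and sampling would have to move closer to listing.
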